## Endpoints

The primary endpoint in this study is the effectiveness (vaginal delivery), the safety (maternal and neonatal morbidity), and the women’s experience and overall satisfaction in immediate postpartum period regarding cervical ripening methods, maternal and obstetric conditions. The secondary endpoint is the impact of cervical ripening on the health-related QOL at 3 months according to the methods.

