**Methods and design:**

The MATUCOL study is a monocentric, prospective, observational study of all consecutive women who required cervical ripening (Bishop score <6) using different methods (DBC, vaginal dinoprostone, oral misoprostol) with a live fetus at term (≥37 weeks) between January 2020 and August 2021. The outcomes will be mode of delivery, maternal and neonatal morbidity, discomfort/pain assessments during cervical ripening, women’s experience and satisfaction, and the impact of cervical ripening on the health-related quality of life at 3 months. If it reports a significant efficacy/safety/perinatal morbidity/women’s satisfaction/quality of life at 3 months post-delivery associated with a method of cervical ripening in a specific situation (gestational and/or fetal disease) using a multivariate analysis, its use should be reconsidered in clinical practice.

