### Statistical analysis

Continuous data will be described by their means ± standard deviations and compared by t tests (or Mann-Whitney tests when appropriate), and categorical data will be described by percentages and compared by χ^2^ tests (or Fisher’s exact tests when appropriate). Maternal and perinatal outcomes will be compared according to cervical ripening method. For the analysis of dissatisfaction in immediate postpartum period, a score < 5 will be considered as a negative result and defined as “dissatisfied”. Maternal QOL at 3 months, assessed by use of EQ-5D-5L scores estimated with the most up-to-date preference-based value set [11,12], will be summarized in each group using mean ± standard deviations and compared between groups using mean differences (99% confidence index). In the five domains of QOL, we will dichotomise into women reporting problems versus reporting no problems and will calculate the outcomes for the different groups. The associations between women’s dissatisfaction at immediate postpartum period and poor QOL at 3 months post-delivery and the characteristics of their pregnancy, cervical ripening methods, labor, and delivery will be then assessed with a multivariate logistic regression model. All analyses were carried out using R software (version 4.0.2). P values <0.05 were considered to be statistically significant.

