## Discussion

This prospective observational study will include all women who will require cervical ripening whatever the method and the indication for IOL. It will assess data about the efficacy, safety, women’s experience of cervical ripening methods and health-related QOL at three months in different maternal and obstetric conditions and in different indications for IOL. The study will then identify factors associated with the efficacy (= vaginal delivery) of cervical ripening, safety, women’s experience and health-related QOL at three months. But, this database will also be used to analyze the efficacy, safety, and women’s experience of methods for cervical ripening in particular indication (gestational or fetal indication) or in particular women (previous cesarean delivery or obese)). We will expect to assess the “ideal” cervical ripening method in specific maternal and/or obstetric conditions. At long term, we also expect a better overall quality of life for the women after cervical ripening due to a personalized strategy.

The woman’s childbirth experience differs according to the type of labor (spontaneous or induced), the mode of delivery (vaginal route, cesarean section) and regarding parity [13]. In case of IOL, it is associated with less satisfaction compared to spontaneous labor [14]. Regarding woman’s experience during IOL, cervical ripening methods were questioned too [15–18]. In a secondary analysis of a randomized controlled trial that enrolled women undergoing IOL with oral misoprostol (n = 273, 54%) or Foley catheter (n = 229, 46%), experience of the duration of labor, pain during labor, general satisfaction with labor, and feelings of control and fear related to their expectation among term women were comparable between both groups. However, women in the Foley catheter group prefer more often to choose a different method for future inductions [18]. A French prospective cohort study including 94 hospitals and 3042 women who had an IOL showed that the determinants of maternal dissatisfaction were unbearable vaginal discomfort, insufficient pain relief during labor, lack of attention to the woman’s demands, a cesarean delivery and severe maternal complications [19]. These findings indicate the importance of advancing understanding of women’s perceptions of their childbirth experience during the perinatal period, specifically in case of IOL.

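### The primary endpoint is three unranked domains tested at P<0.05, and a significant result in any domain in a specific situation is said to justify reconsidering a method

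*Protocol article*

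**What the plan says.** The Endpoints section reads "The primary endpoint in this study is the effectiveness (vaginal delivery), the safety (maternal and neonatal morbidity"), and continues with women's experience and "overall satisfaction in immediate postpartum period regarding cervical ripening methods, maternal and obstetric conditions". The three domains form one primary endpoint. Morbidity and experience are each left as a domain, with no single variable, composite or order. Quality of life at 3 months is secondary.

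The Statistical analysis section ends with "P values <0.05 were considered to be statistically significant". The only stricter level in the text is a 99% interval, and it belongs to the secondary quality-of-life comparison.

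The abstract (Methods and design) states what follows from a significant result. It lists efficacy, safety, perinatal morbidity, satisfaction and quality of life, separated by slashes, and says of a method found significant on these "in a specific situation (gestational and/or fetal disease) using a multivariate analysis, its use should be reconsidered in clinical practice". The Discussion says that the authors expect to assess the ideal "cervical ripening method in specific maternal and/or obstetric conditions", and foresees analyses by indication and in women with a previous cesarean or obesity.

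**The concern.** A primary endpoint should fix, before the data are seen, which result decides the question. Here any of three domains may serve, in the whole cohort or within a condition, each at 0.05. Two consequences follow.

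- **Error rate.** The chance that some comparison reaches P<0.05 when the methods do not differ is far above 5%, and the abstract attaches a conclusion about practice to such a result.
- **Conflict between domains.** A method could show more vaginal deliveries and worse neonatal outcome. The text does not say which result prevails. As worded, the sentence does not even say in which direction a method's use would be reconsidered.

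The within-condition claims raise a related difficulty. Significance in one indication and not in another is not evidence that the method effect differs between them.

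**Working it through.** **The plan's own figure.** The article states no power or overall error rate. Its sample size is a recruitment count: about 40 women a month × 20 months = 800. This reproduces, but it is tied to no endpoint.

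**Inputs from the documents**
- Level per test: 0.05 (Statistical analysis).
- Domains in the primary endpoint: 3 (Endpoints).
- Methods: 3 (Target population).
- Indications: 8 by my count (Trial design and follow-up): prolonged pregnancy, membrane rupture, hypertensive disorders, growth restriction, fetal vitality, diabetes, macrosomia, other.
- Variables under the three domains, by my count from the same section: 1 (vaginal delivery) + 13 maternal + 13 neonatal + 6 experience items = 33. It is 35 if satisfaction is split into induction, labor and delivery.

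**Formula.** With k independent tests and no true differences, P(at least one false positive) = 1 − 0.95^k.

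**Most favorable reading: one global three-method test per domain**
- Whole cohort: 1 − 0.95^3 = 0.143.
- Within each of 8 indications: k = 3 × 8 = 24, and 1 − 0.95^24 = 0.708.
- If only 4 indications counted as situations: 1 − 0.95^12 = 0.460. With 6: 1 − 0.95^18 = 0.603.
- Correlation between domains helps little. A simulation (50,000 runs, three equal groups, equal correlation between outcomes) gave 0.114 for the whole cohort at correlation 0.7, and 1 − (1 − 0.114)^8 = 0.62 over 8 indications.
- Three pairwise tests per domain instead of one global test raise the whole-cohort figure from 0.14 to 0.32 with uncorrelated outcomes.

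**Wider reading: each of the 33 variables tested once, whole cohort**
- Independent: 1 − 0.95^33 = 0.816, with 33 × 0.05 = 1.65 false positives expected.
- Same simulation with correlation: 0.69 at 0.3, 0.53 at 0.5, 0.36 at 0.7.

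**Rare events.** The plan provides for Fisher's exact test. With 267 women per group (800/3) and two groups, its actual size is 0.00002 at an event rate of 0.2%, 0.010 at 1% and 0.032 at 5%. Outcomes such as death or thromboembolism would therefore add almost nothing, and the figures for 33 variables are upper values.

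**After the change**
- One primary outcome with one global test: 0.05.
- Three named co-primaries at 0.05/3 = 0.0167: at most 0.05, and 1 − (1 − 0.0167)^3 = 0.049 if independent.

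**The case against.** Several points on the other side have force.

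- **The count of 33 is mine.** The protocol lists these as variables collected, not as primary tests. Many overlap: blood loss and the two hemorrhage definitions come from one measurement, and cord pH and base excess from one sample. The insertion and in-situ items are asked only of balloon and dinoprostone users. This stands, and it is why the three-domain figure comes first.
- **The abstract's rule is qualified.** It asks for a significant result "associated with a method of cervical ripening in a specific situation (gestational and/or fetal disease) using a multivariate analysis". The Statistical analysis section describes such a model only for dissatisfaction and poor quality of life. Also, not all eight indications are plainly gestational or fetal disease. So eight situations is an assumption. Adjustment for covariates, however, does not control multiplicity.
- **An analysis plan may exist.** Adjustment procedures and interaction tests can be left to it, and their absence here is not the point. The choice of primary endpoint and the sentence on practice are stated in this article.
- **Multiple analyses are a declared purpose of the cohort,** and the limitations paragraph acknowledges selection bias and restricts conclusions to the center's own practice. This limits the harm but does not settle which result is primary.

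A reader might infer that the plan makes a false best method almost certain and would thereby change practice. The documents do not support that. The text says reconsidered, which is weaker. The probabilities above are for at least one false significant result when no method differs, not for naming the wrong method overall. Values near certainty (0.97 or more at correlations up to 0.7) appear only if all 33 variables are tested in all eight indications, and the article does not state that set of tests.

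**Conclusion.** The point holds and should be fixed. The primary endpoint is three unranked domains, the threshold is 0.05 throughout, and the abstract ties a significant result in any domain and situation to reconsidering a method. Under the most favorable reading, the chance of at least one false positive is about 14% in the whole cohort and about 71% over eight indications. Testing 33 variables once each gives up to 82%, or about 36–69% at correlations of 0.7–0.3, and less for rare events.

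These figures assume no true differences, equal group sizes, full-size tests and non-overlapping indication groups. The 14%, 71% and 82% also assume independent outcomes. The conclusion does not depend on the exact value, since the three-domain reading exceeds 5% in every case calculated.

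Confounding by the obstetrician's choice of method is a separate source of false findings that multiplicity control leaves untouched.

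**What to change.** 1. In Endpoints, name vaginal delivery as the single primary outcome, compared by one global three-method test at 0.05. The Discussion already equates it with efficacy: "The study will then identify factors associated with the efficacy (= vaginal delivery) of cervical ripening". Alternatively, name one co-primary variable per domain, each tested at 0.0167. This keeps women's experience at primary level. Any morbidity composite used would need its components defined.
2. Make the remaining outcomes ordered secondary outcomes, or report them as estimates with intervals.
3. Assess conditions through method-by-condition interaction terms, labelled exploratory.
4. Reword the abstract's sentence on reconsidering a method so that any conclusion rests on the confounder-adjusted primary result and its interval. This requires the adjusted model for the primary outcome to be specified, because the article describes one only for dissatisfaction and poor quality of life.

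The cost is wording and one model specification, with no new data and no change to care. Fewer results can be called significant. If vaginal delivery is the sole primary outcome, experience and satisfaction become secondary although they are part of the stated aim.

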Strengths of our prospective observational study include its examination of cervical ripening for variety of maternal, fetal and elective indications at one tertiary hospital. All women with cervical ripening in our center will be cared for by the same obstetric team throughout the period of study, which especially avoided significant variation regarding diagnosis of maternal or obstetric diseases, parameters for cervical examination and IOL management, and obstetric intervention. This will allow for standardized protocols to be followed, thus mitigating differences in outcomes due to variations in clinical practice, increasing the generalizability of our findings. For example, cervical ripening is regularly used in women with one previous cesarean delivery in France [26–28]. In our team, women with one previous cesarean delivery are not contraindicated to mechanical device and its practice is usual and well framed [29]. Other strengths also include performance of individual and prospective collection of data throughout the study period by the same physician and using a standardized protocol according to Bishop score (systematic cervical ripening for IOL with an unfavorable cervix (Bishop score <6), repeating cervical ripening until Bishop score will be above 6). These methodological choices (monocentric design, very large inclusion criteria, outcome, sample size, questionnaires…) are guided by a pragmatic view about cervical ripening, such as all large prospective observational studies in obstetrics [30–33]. These studies allow multiple analyses of data and conclusions about pragmatic management and consequences of some current obstetric conditions that were not adapted to randomized controlled trials (i.e., twins with The JUmeaux MODe d’Accouchement (JUMODA) study) [30,34–39].

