## Conclusions

This study will reveal that some cervical ripening methods will be more effectiveness, safe, with good women’s experiences and QOL at 3 months compared to others regarding maternal and obstetric characteristics.

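### The primary endpoint is three unranked domains judged at an unadjusted P<0.05, and a significant result in any of them is said to justify reconsidering a method

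*Protocol article*

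**What the plan says.** Four statements in the protocol article bear on this.

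- **Endpoints:** "The primary endpoint in this study is the effectiveness (vaginal delivery), the safety (maternal and neonatal morbidity". A third part follows in the same sentence: how women experienced ripening and how satisfied they were soon after birth. Quality of life at 3 months is secondary. Only effectiveness is reduced to one variable. The three parts are neither ranked nor combined.
- **Statistical analysis:** "Maternal and perinatal outcomes will be compared according to cervical ripening method", and "P values <0.05 were considered to be statistically significant". The one departure is the secondary EQ-5D score, which is "compared between groups using mean differences (99% confidence index" in the text. No wider interval or stricter threshold is given for the primary domains.
- **Abstract, Methods and design:** a slash-separated list names efficacy, safety, perinatal morbidity, satisfaction and quality of life. For a significant result the article then states: "associated with a method of cervical ripening in a specific situation (gestational and/or fetal disease) using a multivariate analysis, its use should be reconsidered". The reconsideration concerns clinical practice.
- **Discussion:** the database will also be used for particular indications and particular groups of women. Of large observational studies of this kind the authors write "These studies allow multiple analyses of data and conclusions about pragmatic management". The same section equates efficacy with vaginal delivery.

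**The concern.** A primary endpoint is meant to fix in advance the result on which the main conclusion rests. Here it can rest on delivery mode, on a morbidity item or on a questionnaire score, and each is read against 0.05. The Abstract then attaches a consequence to a significant result in any one domain. The more results that can trigger it, the further the false-positive rate of the whole rule lies above the 5% that a reader associates with P<0.05.

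The article also does not say what to conclude when domains disagree, for example if a method gives more vaginal deliveries but a worse experience. Without an order among the outcomes, emphasis can follow whichever one turned out significant. The Conclusions already expect a positive answer ("This study will reveal that some cervical ripening methods will be more effectiveness, safe"), which makes a fixed order more useful, although that sentence itself is only an editorial matter.

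**Working it through.** **The plan's own figure.** The article gives no power and no overall error rate. Its only planning figure is recruitment: 2,600 × 0.20 / 12 = 43.3 per month, rounded to 40, and 40 × 20 months = 800. This reproduces but does not bear on the error rate.

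**Inputs.**
- Threshold per test: 0.05 (Statistical analysis). Two-sided testing is assumed.
- Methods compared: 3 (Target population).
- Domains in the primary endpoint: 3 (Endpoints).
- Items that could be tested (Trial design and follow-up): 13 maternal, counting second-line haemorrhage therapies as one; 13 neonatal; about 6 questionnaire items; plus vaginal delivery. Total 13 + 13 + 6 + 1 = 33.
- Assumption: some items will be too rare or too overlapping to test separately. The documents give no event rates, so a range of 20 to 33 is used. The value 26 arises if seven items are set aside as rare (second-line therapies, thromboembolism, intensive care, maternal death, intraventricular haemorrhage, seizures, neonatal death).

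**Formula.** If all methods are identical and the k tests are independent, P(at least one P<0.05) = 1 − 0.95^k.

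| Tests k | Reading | 1 − 0.95^k |
|---|---|---|
| 1 | one primary outcome | 5.0% |
| 3 | one test per domain | 14.3% |
| 20 | lower end of item range | 64.2% |
| 26 | after dropping seven items | 73.6% |
| 33 | full list | 81.6% |

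At k = 26 the expected number of false positives is 26 × 0.05 = 1.3.

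**Correlation.** Outcomes in the same women are correlated, so the table overstates the risk for the longer lists. A simulation was run with three equal groups, 26 outcomes, no true difference and 40,000 runs. It used either one overall three-group test per outcome or three pairwise tests.

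| Common correlation | One overall test each | Three pairwise tests each |
|---|---|---|
| 0 | 73.5% | 97% |
| 0.3 | 62% | 91% |
| 0.5 | 48% | 79% |
| 0.7 | 33% | 60% |

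With higher correlation within domains (0.3 to 0.7) than between them (0.1 to 0.2), one overall test each gives 50% to 69%. The pairwise column is relevant because the tests named for continuous data (t and Mann-Whitney) compare two groups, while there are three methods.

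**Subgroups.** Repeating 26 independent tests in two separate groups of women gives 1 − 0.95^52 = 93%.

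**The case against.** The strongest reply is that this is an observational cohort that openly plans many analyses, and that an analysis plan, not shown here, may set an order and an adjustment. That is fair as far as it goes: the absence of a named adjustment method is not the point. The point is what the article does fix, namely three unranked domains called primary, a general 0.05, and a consequence attached to significance. If the study is meant to be exploratory, the Abstract should not attach that consequence.

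Other replies stand in part.

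- **The item count is not the plan's.** Endpoints says only maternal and neonatal morbidity, which could mean composites; the lists are of data collected. Some items overlap (blood loss and the two haemorrhage definitions; cord pH and base excess), and the device-discomfort questions apply to two of the three methods. The figures for 20 to 33 items are therefore conditional. The 14% figure needs only one test per domain.
- **Sparse outcomes are tested conservatively.** In simulation with 267 women per group, the χ² test's actual error was 4.1% at an event rate of 0.5% and 4.7% at 2%. Fisher's test, also allowed, is conservative for sparse outcomes. This lowers the long-list figures somewhat.
- **The three labelled observational studies could be separate error families.** Even so, the 13 maternal items alone give 1 − 0.95^13 = 49%, and six questionnaire items give 1 − 0.95^6 = 26%, if independent.
- **A multivariate analysis is required.** This addresses confounding, not multiplicity, and Statistical analysis specifies such a model only for dissatisfaction and poor quality of life.

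A reader might also infer three stronger things that the documents do not support. First, that everything is tested at 0.05: the EQ-5D score comparison has a 99% interval. Second, that the decision rule amounts to five domains in ten situations, or 50 tests. That count merges the Abstract with the list of indications and with the Discussion, whose analyses in women with a previous caesarean or obesity do not mention quality of life. Third, that a finding on vaginal delivery could not be told from chance: a single test of vaginal delivery keeps its own 5% error, provided it is named in advance as the lead outcome.

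**Conclusion.** The concern holds. The article presents three unranked domains as one primary endpoint, applies an unadjusted 0.05 to them, and lets a significant result in any listed domain prompt reconsideration of a method. Reading the slash-separated list as *any of* is the natural reading; if *all of* was meant, the text needs to say so.

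The best-supported size is about 14% instead of 5%, for one independent test per domain. If items are tested separately, the chance is roughly 64% to 82% under independence for an assumed 20 to 33 items. For 26 items with one overall test each it is about 62%, 48% and 33% at correlations 0.3, 0.5 and 0.7. A false positive somewhere is thus more likely than not under some assumptions and not under others, so it should not be stated as certain. Pairwise or subgroup testing pushes the figures up again. All of them assume no confounding; the free choice of method, which the Discussion concedes, is a separate source of error.

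The Abstract speaks of reconsidering use, which is softer than a practice recommendation, and the Discussion limits conclusions to the centre's own practice. These points reduce the consequence of a false positive, not its probability.

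**What to change.** 1. **Endpoints:** name vaginal delivery, which the Discussion already treats as efficacy, as the single primary outcome for the comparison of methods. One overall three-method comparison at 0.05 then carries a 5% false-positive risk.
2. **Secondary outcomes:** place morbidity and overall satisfaction here, and apply a multiplicity adjustment if they are to support conclusions. Holm is one option. Keeping three co-primary outcomes, one per domain, at 0.05 / 3 = 0.0167 each would also control the error.
3. **Exploratory:** label the remaining outcomes and all analyses by indication or type of woman as such.
4. **Abstract, Methods and design:** reword so that reconsidering a method rests on the primary result or on adjusted secondary results, not on any P<0.05, and say how conflicting domains will be read.

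Neutral wording in the Conclusions would be a sensible editorial companion. The cost is wording in the protocol or analysis plan, with no new data; the downside is that fewer results can be called significant.
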